### Plans to give access to the full protocol, participant-level data, and statistical code {31c}

The datasets analyzed during the current study and statistical code are available from the corresponding author on reasonable request, as is the full protocol.

## Oversight and monitoring

### Composition of the coordinating center and trial steering committee {5d}

The MOVIS Coordinator Center (MCC) aimed to provide clinical, scientific, and organizational leadership to the MOVIS initiative, including facilitating scientific collaboration across the institutions involved (Hospital of Urbino, GYM at the School of Health and Physical exercise of the University of Urbino and The National Institute of Oncology in Milan. To this end, the MCC was organized into different cores to respond to the need of disciplinary integration and collaboration: (1) leadership and administration; (2) developmental projects; (3) education and training: (3a) nutrition issues, (3b) nutrition issues, (3c) psychological issue; (4) case report format (CRF) data mobility and analyses; and (5) integration and self-evaluation.

Each core is led by a senior clinician or researcher and is a member of the project staff. Table 1 summarizes the MOVIS CC core and goals.

**Table 1 Tab1:** MOVIS Coordination Center cores and goals

CC core	CC core goal
1) Leadership and administration	Facilitate interdisciplinary research through scientific leadership and organizational support with an emphasis on efficient communication, coordination efforts, and expanded scientific collaboration across different research institutions; create opportunities to disseminate results by congress and publications; facilitate contacts between professional staff to allow for efficient interactions, consultations, and oversight functions.
2) Developmental projects	Coordinate the collaborative research proposed during the project; create and manage logistical infrastructure.
3) Education and training	Create the condition to carry out the educational change in lifestyle with the expert in nutrition exercise and with the support of the psychologists.
4) Case report format (CRF) data mobility and analyses	Design a CRF and assess the safety and efficacy of the intervention accurately respect the principal and secondary outcomes, collection of data, and research data management in accordance with the study protocol compliance. Test the hypothesis or answer the trial-related questions.
5) Integration and Self-Evaluation	Facilitate integration and evaluation of in collaboration with the Research Centers.

### Composition of the data monitoring committee, its role, and reporting structure {21a}

A panel of seven (*n* = 7) experts was organized comprising statisticians and experts in lifestyle clinical trials. Twelve outcomes and measures were discussed by the panel at the beginning of the research plan. A subgroup of experts (2–3 persons including a researcher/clinician and a technician) was identified for each task. The expert panel got an agreement with the collaborators and defined the meeting planning and the management of ethical issues. The expert panel planned the overall responsibility for the trial for sponsors and associations. The MoviS TSC discusses the review of data, sharing requests, indemnity, lifespan, and general administration, and ensures that the trial is conducted following rigorous standards.

### Adverse event reporting and harms {22}

Adverse events, including serious adverse events, will be collected throughout the study period, beginning from the time the participants sign the ICF until 2 weeks after the end of the study. All adverse events persisting at the time of study completion will be followed by the investigators through contact with the participant until resolution or stabilization, or the participant is lost to follow-up and cannot be contacted. The outcomes of the adverse event will be documented in the participants’ source documents. The investigators will report any serious adverse events that occur after the protocol-specified reporting period if, according to the investigators’ assessment, there was a reasonable possibility that the serious adverse event was related to any study procedures. Specific pre-specified adverse events include acute osteoarticular pathology, experiencing arthralgia, gastrointestinal eating disorders, and inhibition of cardiorespiratory fitness.

### Frequency and plans for auditing trial conduct {23}

The Data Monitoring Committee was not considered as this is a low-risk intervention.

### Plans for communicating important protocol amendments to relevant parties (e.g., trial participants, ethical committees) {25}

Before applying any amendments to the study protocol, the proposed amendment will be submitted to the ethical committee. Then, after approval from the ethical committee, the amendments will be communicated to the participants, who will sign an amended informed consent if they are willing to continue the study.

## Dissemination plans {31a}

Results obtained from this trial will be disseminated through participation in national and international conferences with abstracts, posters, and oral communications. Definitive results will be published in peer-reviewed international journals. Moreover, dissemination events will be organized in order to make available the knowledge improvement about the benefits of supervised exercise to healthcare workers, BC survivors, and all interested people.

## Discussion

In the MoviS Trial, we will estimate the effectiveness of a lifestyle intervention based on proper nutrition (Mediterranean diet) and exercise (supervised aerobic exercise) on the QoL of inactive BC survivor women. In addition, we will investigate the cardiometabolic effect and the feasibility of a structured exercise program in BC survivor women recruited at the Oncology Unit of Urbino.

Previous RCTs in the field of exercise-oncology have shown beneficial effects of lifestyle changes, in particular on the risk of distance recurrence [18] and improvement of the quality of life [32–37]. Many beneficial effects are also attributable to the potential effect of exercise and a correct diet in mitigating the side effects due to surgery and adjuvant therapy (e.g., chemotherapy, radiotherapy, immunotherapy, and hormone therapy), such as physical and psychological deconditioning [38, 39]. However, the questions to improve the approach of women with BC still need clear answers. The existing RCTs in the field of exercise-oncology described how different types of exercise interventions can be beneficial for physical function, cancer-related fatigue, pain, and muscle strength [40, 41]. Such effects are due, in part, to physical exercise leading to improvements in physical fitness, cardiorespiratory function, muscular endurance, and body composition [8]. Emerging evidence suggests the beneficial effects of the exercise are greater if the exercise is supervised and follows the key components of exercise (i.e., frequency (F), intensity (I), time (T), type (T), volume (V), and progression (P) over time, namely the FITT-VP principle) [20, 42]. In this context, it is well known that the adherence of BC survivors to exercise is low [43] and that engagement to motivation to exercise plays an important role in promoting and adhering to physical activity guidelines in BC survivors [44–46]. Indeed, in the present study, a mixed approach (composed of directly and remotely supervised exercise sessions) will be adopted to evaluate if the direct specialist supervision combined with the education and active involvement of the participants in their training, which will be partially performed autonomously according to personalized indications, can provide beneficial effects and high adherence both in short and long terms. Additionally, it is worth noting that the mixed approach not only might have the advantage related to the active involvement of the participants and the elevated level of supervision, which are crucial to increasing the adherence to an exercise program and obtaining beneficial effects from it, but it can also be a cost-effective approach compared to a fully supervised intervention, which requires a fitness facility and exercise specialist to always be present.

This multidisciplinary project is based on the dynamic and structured interaction between different expertise, such as those of medical oncologists, nutritionists, exercise experts, and biochemists/molecular biologists, and is part of innovative research projects related to wellness, health, and biomedicine. For these reasons, results will have an impact both on clinical practice and on the area of personal well-being. This approach can be particularly useful for patients reluctant to start physical activity programs because they fear that an intense activity may worsen BC-related symptoms, such as fatigue and pain, as well as to undertake a dedicated nutritional strategy [9].

The success of this project will give a double support to the oncologist’s in-patient management and to the patients in overcoming the barriers related to the management of a correct lifestyle. The existence of a multidisciplinary team working in synergy from a holistic point of view allows us to manage, to face, and to overcome different and specific needs of patients. Therefore, creating a safe environment represents an important action plan in the care of cancer patients, and promoting a healthy lifestyle in clinical practice reduces risk factors involved in BC recurrence and ensures psycho-physical well-being.

Despite its potential strengths mentioned above, the proposed MOVIS trial presents certain limitations. The first one and more actual is the exceptional pandemic context where the experimentation has been developed. During COVID-19 restrictions, cancer patients and survivors easily regress to sedentary lifestyles [47], which results in declining health and quality of life, particularly for patients undergoing treatment or suffering adverse effects of treatment. Home confinement made it more difficult to reach the guidelines of oncological prevention for both nutrition and regular PA [47]. The final analysis, thus, could potentially and partially be affected by the COVID-19 pandemic.

Moreover, in the present project, although it is recommended that exercise programs include resistance exercises [8, 20], the participants of both groups will solely receive generic indications regarding the importance and guidelines of resistance exercises and flexibility training during the counseling sessions, but they will not receive any supervision or prescription for those two exercise modalities. Therefore, the inferences on the possible short- and long-term differences between the two arms, hence the effect of the mixed directly and remotely supervised exercise intervention, will only be applicable and valid for aerobic exercise; hence, future studies should assess the efficacy of these types of interventions and supervisions in exercise programs involving both aerobic and resistance exercise or resistance exercise only.

Additionally, it is worth noting that RCT interventions in the field of exercise oncology have several limitations, such as drop-out and loss of follow-up of patients during the entire course of the study. For this reason, we estimate an expected drop-out of 30% for a total of 172 patients after the 12-week interventions, which will probably increase over the 2 years of follow-up. To ensure that the drop-out rate is not affected by the present study design and consequently affects the results of the present study, trial retention will be scored as the rate of drop-out after signing informed consent for the study and registered for both groups. Then, exploratory analyses will be performed to assess if several factors (e.g., trial arm, clinical, and characteristics) affected the drop-out rate.

Moreover, since the control arm is aware of participating in the trial and received counseling regarding the benefits of physical activity, a possible increase in physical activity levels in the control arm, which could be caused by several factors (e.g., motivation to change their lifestyle after diagnosis), could happen and dampen the differences between the two arms regarding their physical activity levels. However, due to the well-known beneficial effect of physical activity in breast cancer survivors, for ethical reasons, we have decided to decrease the barriers to perform physical activity and promote it also in the control arm. Notwithstanding, physical activity levels will be evaluated using the IPAQ and the Sensewear armband and their effect will be evaluated as a possible confounding variable of this study. The ethical decision of promoting physical activity also in the control arm was made necessary because using other types of study design (e.g., using a wait-list control group) would have made impossible to obtain longer term follow-up without compromising the optimal patients care.

Patients are enrolled within 12 months after diagnosis because at this time most of these patients have finished their primary treatment (e.g., chemotherapy and/or radiotherapy) but most of these continuing the hormone therapy for at least 5 years. In this period, the impact of diagnosis and neoadjuvant/adjuvant treatment on normal daily living (e.g., complaints of fatigue, impaired quality of life) become more impactful. Although several studies have shown that exercise has a beneficial effect on the QoL and treatment-related symptoms of patients with breast cancer in this period, adherence to nutrition and exercise guidelines is low. This study provides the opportunity to assess the feasibility of a RCT design in the field of exercise-oncology as a model from a single institution and examine the effectiveness of a lifestyle intervention based on early patient support and mixed approach that including nutritional and exercise counseling, and specific therapeutic exercise (12weeks of supervised aerobic exercise). The proposed intervention will allow to examine its effect on the QoL and other several health-related parameters of patients with breast cancer in the short term (6 months) and medium-long term (12 and 24 months).

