**Methods:**

One hundred seventy-two BC survivor women, aged 30–70 years, non-metastatic, stage 0–III, non-physically active, 6–12 months post-surgery, and post chemo- or radiotherapy, will be recruited in this study. Women will be randomly allocated to the intervention arm (lifestyle recommendations and MoviS Training) or control arm (lifestyle recommendations). The MoviS training consists of 12 weeks of aerobic exercise training (2 days/week of supervised and 1 day/week of unsupervised exercise) with a progressive increase in exercise intensity (40–70% of heart rate reserve) and duration (20–60 min). Both arms will receive counseling on healthy lifestyle habits (nutrition and exercise) based on the World Cancer Research Fund International (WCRF) 2018 guidelines.

The primary outcome is the improvement of the QoL. The secondary outcomes are improvement of health-related parameters such as Mediterranean diet adherence, physical activity level, flexibility, muscular fitness, fatigue, cardiorespiratory fitness (estimated maximal oxygen uptake), echocardiographic parameters, heart rate variability (average of the standard deviations of all 5 min normal to normal intervals (ASDNN/5 min) and 24 h very low and low frequency), and metabolic, endocrine, and inflammatory serum biomarkers (glycemia, insulin resistance, progesterone, testosterone, and high-sensitivity C-reactive protein).

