
Other pre-specified outcome measures:20.Diet habits: change in dietary intake assessed by questionnaire (14-item Mediterranean diet adherence screener, MEDIET) through the DIANAWeb platform. Higher levels (8–9 or >10 points in the 14-item score) indicate adherence to the Mediterranean diet.21.Physical activity level: change in physical activity level assessed by the sensewear armband activity monitor and by the international physical activity questionnaire (IPAQ). The output of both assessments expressed in metabolic equivalents (METs)-min/week.

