Psychological well-being will be assessed through the evaluation of mood profile change (Profile of Mood States (POMS) questionnaire). The analysis of metabolic, hormonal, and inflammatory risk factors will include Homeostatic Model Assessment for Insulin Resistance (HOMA-IR) Index, insulin-like growth factor (IGF-1), and C-reactive protein.

Gut microbiota will be assessed by the analysis of microbial diversity (NGS of the V3–V4 region of the 16S rDNA gene). Osteoporosis level will be assessed by computerized bone mineralometry (*T*-score). Recurrences free interval defined as time from registration to time of documented recurrent disease will be assessed.

Diet habits, physical activity level, pharmacological treatments, and comorbidity will be recorded as confounding factors and covariates. Change in dietary intake will be assessed by a questionnaire (14-item Mediterranean diet adherence screener, MEDIET) through the DIANAWeb platform [22, 30]. Change in physical activity level will be assessed by the SenseWear armband activity monitor (BodyMedia Inc., Pittsburgh, PA) that participants will wear for at least 5 consecutive days (24 h a day) and by the International Physical Activity Questionnaire Short Form (IPAQ-SF) [16, 17]. The output of both assessments will be expressed in metabolic equivalents (MET∙min∙week^−1^).

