### Methods for additional analyses (e.g., subgroup analyses) {20b}

An exploratory analysis will be conducted through the principal component analysis (PCA), in order to highlight any subgroups showing a homogeneous response pattern. Additional exploratory analyses will also be performed using participants’ characteristics (e.g., age, fitness status, physical activity level, and metabolic and clinical profile) as covariates to assess possible underlying confounding variables on the primary and secondary outcome results.

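### Physical activity during the trial is labelled a confounder although the allocated arm changes it; exploratory adjustment should use T1 values only

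*Protocol article*

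**What the plan says.** The Protocol article gives physical activity and diet two roles.

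**As outcomes.** Outcomes {12} includes, among the other pre-specified measures, "change in physical activity level assessed by the sensewear armband activity monitor" and by questionnaire, and also "Diet habits: change in dietary intake assessed by questionnaire". The abstract puts both a tier higher: "The secondary outcomes are improvement of health-related parameters such as Mediterranean diet adherence, physical activity level".

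**As confounders or covariates.** Section {18a} states: "Diet habits, physical activity level, pharmacological treatments, and comorbidity will be recorded as confounding factors and covariates". The same paragraph then describes these measures as changes, for example "Change in physical activity level will be assessed by the SenseWear armband activity monitor". Section {20b} plans exploratory analyses that use participant characteristics, physical activity level among them, "as covariates to assess possible underlying confounding variables on the primary and secondary outcome results". The Discussion considers that counselled control-arm women may become more active and so narrow the contrast in activity between the arms; its response is that "physical activity levels will be evaluated using the IPAQ and the Sensewear armband and their effect will be evaluated as a possible confounding variable".

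The primary analysis in {20a} is a mixed-design ANOVA of arm by time, T1 to T2, and names no covariate.

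**The concern.** A confounder of the arm comparison would have to be a cause of both allocation and outcome. Randomisation rules that out for anything that happens after allocation. Activity during the trial is what the training is meant to raise, so it lies on the path from arm to quality of life (QoL). Extra activity in the control arm is a result of the counselling that the protocol deliberately gives that arm, and so belongs to the comparator.

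An arm effect adjusted for on-trial activity answers a different question: at best, what the arm does other than through activity. It can also pick up bias from causes shared by activity and QoL, which randomisation does not balance once activity is held fixed. If such an estimate is smaller than the unadjusted one and is reported under the label of confounding, a reader could conclude that the benefit was spurious when it was simply working through activity.

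**Working it through.** **1. The plan's own figure.** Inputs from Sample size {14}: improvements of 15.1 (SD 17.7) and 6.1 (SD 17.1), alpha 0.05, power 0.80, drop-out 30%. The test is two-sided according to {20a}.
- Difference: 15.1 − 6.1 = 9.0.
- Pooled SD: √[(17.7² + 17.1²)/2] = √302.85 = 17.40.
- Normal approximation: n = 2 × (1.960 + 0.842)² × 302.85 / 81 ≈ 58.7, so 59 per arm. The exact t-test gives 59.67, so 60 per arm, with power 0.802.
- Drop-out: 60 / 0.70 = 85.7, so 86 per arm and 172 in total.

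The stated 60 per arm and 172 reproduce. They refer to the contrast without covariates.

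**2. Which time point each statement means.**
- *Discussion.* The worry is a rise in control-arm activity after counselling. A baseline value cannot address it. Eligibility {10} also requires women who have not been regularly active for at least 6 months, so baseline activity is restricted by design. This statement concerns on-trial activity.
- *{18a}.* The covariate label is followed by a description in terms of change. A change from T1 includes a post-randomisation value.
- *{20b}.* No time point is given. Activity stands beside age and clinical profile, so a baseline reading is possible. Fitness status and metabolic profile stand in the same list, and cardiorespiratory fitness and HOMA-IR are secondary outcomes in {12}, so the missing time point matters for them too.

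**3. What adjustment would do.** Take a linear model: QoL change = a + c × arm + b × activity + error, with an arm difference g in activity.
- Total effect: c + b × g = 9.0.
- Share through activity: m = b × g / 9.0.
- Arm effect adjusted for activity: c = 9.0 × (1 − m).

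The documents do not give m. Over an assumed range:

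| Assumed m | Unadjusted effect | Adjusted effect |
|---|---|---|
| 0 | 9.0 | 9.0 |
| 0.25 | 9.0 | 6.75 |
| 0.50 | 9.0 | 4.5 |
| 0.75 | 9.0 | 2.25 |

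A simulation with 60 per arm, SD 17.40 and an assumed arm difference in activity of 0.5 or 1.0 SD agreed to within sampling error: adjusted means of 6.7 to 6.8, 4.4, and 2.2 to 2.3 for the last three rows. Unadjusted means stayed at 8.9 to 9.1, with power about 0.80. The table contains no common cause of activity and QoL; such a cause could move the adjusted estimate either way.

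**The case against.** The strongest reply is that no section writes down a model of the arm effect adjusted for post-T1 activity. Section {18a} concerns data collection, the Discussion passage is about limitations and names no method, and {20b} is exploratory and can be read as using baseline characteristics. A variable may also serve as an outcome in one analysis and, measured at baseline, as a covariate in another, so the double listing alone is no contradiction.

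Much of this stands. If {20b} means T1 values, that analysis is harmless. The case is also thin beyond activity: both arms receive the same dietary counselling, {20b} does not name diet, and for drugs and comorbidity {18a} says only that they are recorded as covariates.

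The reply does not remove the Discussion statement, which makes sense only for activity during the trial, or the description in {18a} of the same covariates as changes.

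A reader might infer that the trial's main result would be diluted, or that its power would fall well below 0.80. The documents do not support that: the primary ANOVA carries no covariate, and no power is claimed for any adjusted analysis. Nor do they support saying that an adjusted analysis will show a small or absent effect. With m = 0 the estimate stays at 9, and the calculation returns whatever share is put in.

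**Conclusion.** The point holds as one about the exploratory analyses and their interpretation. On-trial physical activity is called a possible confounder in the Discussion and, described as a change, a covariate in {18a}, although it is affected by allocation and is itself a listed outcome. Conditioning the arm effect on it would not estimate the total training effect on QoL or the secondary outcomes, and the label invites the wrong conclusion if the estimate shrinks.

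The primary analysis, the sample size and the stated power are unaffected. The size of any attenuation is unknown; 9 × (1 − m) shows its form under a linear model with no shared causes of activity and QoL, and m is an assumption. The conclusion that activity is a mediator rests on the protocol's own aim of changing lifestyle through the programme. It is firm for activity and weaker for diet.

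**What to change.** - In {18a}, {20b} and the Discussion, state that covariates in the exploratory adjusted analyses are T1 values only.
- Report post-T1 activity, and diet, by arm as outcomes. This shows any control-arm uptake directly. Give them the same outcome tier in the abstract and in {12}.
- If the role of on-trial activity is of interest, plan a separate analysis labelled as mediation or control-arm contamination, with its assumptions stated, and drop the term confounding for it.

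The cost is wording only. Change scores in activity and diet already require a T1 value, so no new data are needed, and neither the sample size nor the primary analysis changes.
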